#### Adverse effects

taVNS is, as already described, a non-invasive method to stimulate the auricular branch of the vagal nerve.^5^,^7^ In 2023, Tan *et al* published a systematic review and meta-analysis showing the safety of taVNS application,^4^ see also pooled data analysis by Giraudier *et al.*^5^ In the case of the occurrence of any adverse events during the planned study (for example, experience of pain, itching of the skin, skin irritation, dizziness, etc), a corresponding report will be created by the research assistant. The adverse event will be evaluated towards a potential causal relationship to the treatment and the severity of the adverse event.

### Randomisation

Subjects will participate in two study sessions (day 1 and day 2), in which the participants will receive either SHAM stimulation or verum stimulation (cross-over design; stimulation will be counterbalanced across sessions). The respective stimulation condition in the first session will be determined using a lottery procedure (online randomisation tool). In summary, each participant will switch from verum to SHAM and vice versa.

### Study schedule

#### Intervention groups

This study comprises two groups, PwRRMS (n=30) and healthy controls (n=30). Both groups will undergo the same study schedule (figure 1). Patients will be blinded for the procedure using a lottery procedure to decide whether the participants start with SHAM or verum stimulation.

**Figure 1 F1:**
[figure not shown]
Study schedule. PwMS, people with relapsing remitting multiple sclerosis, taVNS, transcutaneous auricular vagus nerve stimulation.

#### Baseline assessment

At the beginning, a medical interview will be conducted in which the relevant epidemiological and demographical data, including age and sex, are collected. Following the interview, a neuropsychological examination will be carried out, consisting of SDMT, BDI-II, FSMC and EDSS (the latter only used in PwRRMS).

#### Intervention

After baseline assessment, consisting of neuropsychological assessment (duration: about 30 min), stimulation (SHAM stimulation or verum stimulation) will be applied for 15 min followed by a second neuropsychological assessment under stimulation. In the first 15 min of stimulation (SHAM stimulation or verum stimulation), the participant will sit relaxed in a chair without a specific task. When the second neuropsychological assessment is completed, taVNS will be applied for another 5 min without a specific task.

#### Follow-up and further investigations

There will be a wash-out period of at least 7 days to eliminate possible long-term effects of stimulation. The second assessment on study day 2 will follow the same protocol as study day 1.

### Outcomes

#### Primary

The primary outcome measurement will be the processing speed in PwRRMS (SHAM stimulation vs verum stimulation), operationalised by the SDMT accuracy (total number of correct answers in 90 s).

#### Secondary

Exploratory outcome measurements will be:

The processing speed in healthy controls in relation to the stimulation method (SHAM stimulation and verum stimulation), operationalised by the SDMT accuracy.The difference in the change in processing speed (SHAM stimulation vs verum stimulation) between the groups (PwRRMS/controls).The association between disease-related variables (disease severity, fatigue and depression) and the change in processing speed.

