Recent studies provide evidence for taVNS to express beneficial effects on cognitive outcomes in healthy adults, showing improvements, for example, in spatial working memory, executive functions, learning or motivation after taVNS compared with control conditions.^23^,^30^ Furthermore, there are first results showing an improvement in cognition when long-term stimulation (n=76; 2-week taVNS, daily use for 4 hours/day) is used in healthy adults.^31^

Moreover, the effect of taVNS on cognition has also been assessed in neurological conditions, including epilepsy, stroke and mild cognitive impairment due to neurodegenerative disorders.^32^,^34^

Until now, the effect of taVNS on processing speed in PwRRMS has never been assessed. Based on the already existing promising effects on cognitive domains in other diseases due to neurotransmitter changes and the cortical and subcortical alterations due to the neurotransmitter modification, taVNS might have the potential to alter processing speed in PwRRMS.

In 2020, Grothe *et al* revealed the functional representation of the Symbol Digit Modalities Test (SDMT) in PwRRMS. The results showed an activation of frontal, occipital, parietal and cerebellar areas under performance of the SDMT.^35^ The neuroanatomical overlap between cortical areas that are activated due to taVNS and the areas that are crucial for processing speed performance (cerebellum and prefrontal cortex) might support the hypothesis that taVNS can alter processing speed performance.^14 21 35^

Based on the neurotransmitter network alterations and the overlap between the cortical and subcortical areas that are affected by taVNS and are responsible for processing speed performance in PwRRMS, the aim of this study is to assess the effect of taVNS on processing speed in PwRRMS (primary). Furthermore, the association between disease-related variables (disease severity, fatigue and depression) and the change in processing speed will be evaluated (secondary). This protocol is intended to describe the background, planned methods and procedures for the proposed study.

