## Discussion

taVNS is an already established non-invasive treatment option for depression or epilepsy.^51^,^53^ Recent studies investigating the effect of taVNS on cognition in healthy subjects provide preliminary evidence for its potential to also improve cognitive functions (eg, improvement of executive functions and spatial working memory).^23 24^

Mechanistically, taVNS might mediate its effect on cognition via different neurotransmitter systems and thus be a promising treatment option for cognitive impairments.^14 21^ For example, taVNS leads to an activation of the NTS which, in turn, leads to a stimulation of the locus caeruleus (release of norepinephrine).^54 55^ The increased levels of norepinephrine have widespread effects on cerebral structures that are important for different cognitive functions (eg, enhanced synaptic plasticity in the hippocampus).^56^

Furthermore, fMRI data revealed an anatomical overlap between SDMT performance and areas that are activated through taVNS application.^35^ A neurophysiological activation of these structures (such as the cerebellum or parietal cortical areas) might lead to an alteration in SDMT performance in PwRRMS.

Based on these findings, we hypothesise that taVNS will significantly improve processing speed in PwRRMS as well as in healthy controls (primary). Moreover, we will assess whether the stimulation-induced effect is also modulated by additional disease variables like disease severity, fatigue or depression (secondary).

To the best of our knowledge, this is the first study investigating the effect of taVNS in non-motor symptoms in PwRRMS (processing speed). With this study, we will determine whether taVNS improves an important aspect of cognitive function, that is, processing speed.

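### The third secondary outcome, as worded, is neither referenced to SHAM nor limited to PwRRMS, so it does not test whether disease variables modulate the taVNS effect

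*Protocol article*

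**What the plan says.** All places are in the protocol article.

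- **Outcomes, Secondary, third item:** "The association between disease-related variables (disease severity, fatigue and depression) and the change in processing speed". The whole list is labelled exploratory.
- **Introduction, closing aims:** the same wording, "the association between disease-related variables (disease severity, fatigue and depression) and the change in processing speed will be evaluated (secondary".
- **Outcomes, Secondary, second item:** "The difference in the change in processing speed (SHAM stimulation vs verum stimulation) between the groups (PwRRMS/controls". Here the contrast and both groups are named.
- **Outcomes, Primary:** "The primary outcome measurement will be the processing speed in PwRRMS (SHAM stimulation vs verum stimulation". Here too the contrast and the population are named.
- **Discussion:** the secondary aim becomes a question about effect modification, "we will assess whether the stimulation-induced effect is also modulated by additional disease variables like disease severity, fatigue or depression".
- **Data analysis:** one linear mixed model serves the primary and secondary outcomes. Time is pre versus during. Stimulation, group and session order are fixed effects. Age, fatigue, depression and severity are fixed effects labelled as control variables. No interaction is named.
- **Baseline assessment:** testing is described as "consisting of SDMT, BDI-II, FSMC and EDSS (the latter only used in PwRRMS". Fatigue and depression scores therefore exist for controls as well; EDSS does not.

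**The concern.** Because time is pre versus during, every session yields a change in SDMT score, including the SHAM session. That change contains task familiarity, tiring and any response to stimulation. Only its difference from the SHAM-session change isolates the stimulation effect. Fatigue, depression and disability could plausibly be related to practice and tiring whether or not taVNS does anything.

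The outcome as worded and the question in the Discussion are therefore different quantities. An association with an unreferenced change can be clearly positive when no disease variable alters the response to taVNS. Reported under the Discussion's aim, it would read as a finding about who responds.

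The unstated population adds a smaller problem for fatigue and depression. If patients and controls are pooled, the association partly restates the patient-control difference that the second secondary item already addresses.

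**Working it through.** **1. Is there a figure to reproduce?** No. The Sample size section gives 30 PwRRMS and 30 controls by reference to other studies, with no effect size, SD or power. For scale, 30 patients at two-sided 5% have 80% power for a correlation of tanh((1.960 + 0.842)/√27) = 0.49.

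**2. The wording, side by side.**

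| Place | SHAM contrast named | Population named |
|---|---|---|
| Primary outcome | yes | PwRRMS |
| Secondary item 2 | yes | PwRRMS and controls |
| Secondary item 3 | no | no |
| Introduction, same aim | no | no |
| Discussion, same aim | implied (stimulation-induced effect) | no |

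**3. Why the reference matters.** Let F be standardised fatigue, V the pre-to-during change under verum and S the change under SHAM, each with unit variance. Suppose there is no modulation, so F has the same correlation r with V and with S. Then cov(F, V) = r, but cov(F, V − S) = r − r = 0. The shared association stays in the bare change and cancels in the difference.

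**4. Size for a verum-only change.** Inputs: n = 30 (Sample size section), significance level 5% (Data analysis section, taken as two-sided), and r assumed. By Fisher's z, the chance of a significant result is approximately Φ(√27 · atanh r − 1.96), with a negligible lower-tail term:

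- r = 0.2: 5.196 × 0.2027 = 1.053, giving 18%
- r = 0.3: 5.196 × 0.3095 = 1.608, giving 36%
- r = 0.4: 5.196 × 0.4236 = 2.201, giving 60%
- r = 0.5: 5.196 × 0.5493 = 2.854, giving 81%

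Simulation with a Pearson test agrees. The range for the averaged change covers a residual correlation of 0 or 0.3 between the two sessions.

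| Assumed r (either sign) | Verum-only change | Change averaged over both sessions | Verum minus SHAM |
|---|---|---|---|
| 0 | 5% | 5% | 5% |
| 0.2 | 18–19% | 26–32% | 5% |
| 0.3 | 37% | 51–63% | 5% |
| 0.4 | 61–62% | 78–86% | 5% |
| 0.5 | 83% | 94–98% | 5% |

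The modulation effect is zero in every row, so every rejection is false as a statement about modulation.

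**5. Does the stated model supply the reference?** Not as described. A main effect of fatigue shifts the SDMT level equally at all four measurements (pre and during, in two sessions). Whether fatigue alters the stimulation effect is carried by fatigue × time × stimulation.

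**6. Pooling the groups.** Assume no modulation within either group, a 1.5 SD group difference in fatigue, and a group difference of 0.3, 0.5 or 0.8 SD in the SHAM-referenced effect. An unadjusted pooled correlation in 60 subjects is then significant in 10%, 20% or 41% of trials, against about 5% in PwRRMS alone. These inputs are also assumptions.

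**The case against.** **Intent.** The second secondary item introduces the change together with its SHAM-versus-verum qualifier, and the third follows directly with the definite article. The Discussion names the stimulation-induced effect. The natural reading is that a SHAM-referenced change was meant. This stands as evidence of intent. It does not reach the Introduction, where the bare wording has no such antecedent, and it leaves the outcome definition itself incomplete.

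**Population.** The item speaks of disease-related variables, and EDSS is used only in patients. This largely stands. The gap is real only for fatigue and depression. Group is a listed fixed effect, so an unadjusted pooled correlation is not the stated analysis. A group main effect would not, however, absorb a group difference in the stimulation effect.

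**Stated analysis.** A reader might infer that a verum-only analysis is planned. The article does not support that: it proposes no such analysis, and its mixed model uses both sessions. A reader might also infer that the final model will contain no interactions. That goes too far as well. The article names none even for the primary comparison, and a condensed article may leave such terms to a fuller plan. What is stated is the role of the disease variables as control variables, and that role does not match the Discussion's question.

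**Assumed correlations.** The article gives no correlation between fatigue and the within-session change. It describes the FSMC as measuring trait fatigue, and alternate SDMT versions are used to limit learning. The true value may be small, and at r = 0 the excess vanishes. This stands. Alternate versions limit item learning but do not remove task familiarity or tiring.

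**Conclusion.** The point holds as a badly fixed definition of one exploratory outcome. Taken literally, the Introduction and the third secondary item ask about an unreferenced change, and the Data analysis section gives the disease variables only an adjusting role. Together these do not test the modulation question posed in the Discussion.

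The false-positive figures of about 19% to 83% apply only if a verum-only change is analysed and fatigue correlates 0.2 to 0.5 with the change equally in both conditions. They show what the wording permits and do not forecast what will be reported. Only the direction is general: any non-zero shared association inflates a bare-change result and cancels against SHAM.

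A reader might infer that a false responder conclusion will follow, or that the trial's main result is compromised. The documents support neither. No text commits to ignoring SHAM, and the primary outcome carries its own SHAM contrast. This is a cheap improvement.

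**What to change.** Define the third secondary outcome as the association, within PwRRMS, of EDSS, FSMC and BDI-II at the first baseline with the verum-minus-SHAM difference in the pre-to-during SDMT change. Naming the first baseline matters because study day 2 repeats the day 1 procedure.

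In the Data analysis section, state that this is tested as the variable × time × stimulation interaction. Align the Introduction, Secondary outcomes, Data analysis and Discussion to the same wording.

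The cross-over already gives each participant a SHAM-session change, so no new data, visits or participants are needed. The price is precision. With equal variances and a between-session correlation ρ, the difference has variance 2(1 − ρ) times that of a single-session change. Intervals are therefore wider whenever ρ is below 0.5, by a factor of √2 ≈ 1.41 at ρ = 0.

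Reporting the association with the SHAM-session change alongside, as a negative control, is optional.

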### Statistical analysis

#### Sample size

To the best of our knowledge, there is no study investigating the effect of taVNS on processing speed in PwRRMS. Based on other studies assessing the effect of taVNS on non-motor symptoms like attentional processes or working memory, we plan a sample size of 60 subjects (30 healthy controls and 30 PwRRMS).^33 49 50^

#### Data analysis

Statistical analysis will be conducted using SPSS Statistics V.25 (IBM SPSS Statistics for Mac, V.25.0. Armonk, NY: IBM Corp). With a total number of n=30 in each study arm, a normal distribution can be assumed. Based on this, normally distributed variables will be presented as mean±SD. Non-normally distributed variables will be presented as median and (IQR). A linear mixed model will be performed for the primary/secondary outcomes using ‘time’ (pre vs during), ‘stimulation’ (taVNS vs sham), ‘group’ (MS vs controls), ‘session order’ (Session 1 vs Session 2) and ‘control variables’ (age, fatigue, depression and severity) as fixed, ‘participant’ as random effects. A significance level of 5% will be used to test the hypotheses.

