## Introduction

 Relapsing remitting multiple sclerosis (RRMS) is one of the most prevalent neurological disorders, especially in young adults.^1^ The disease can lead to many different neurological signs and symptoms, such as paresis or hypoaesthesia, as well as cognitive impairment occurring in 40%–70% of people with RRMS (PwRRMS).^2^ The most prevalent impaired cognitive domain is processing speed, which has a significant impact on quality of life.^3^ While highly effective immunomodulatory drugs are available to suppress disease activity, there are no specific treatment options for cognitive impairment.

A new therapeutic approach might be transcutaneous auricular vagus nerve stimulation (taVNS), which is a safe, non-invasive method that stimulates the auricular branch of the vagus nerve.^4^,^7^ Stimulation of the auricular branch of the vagus nerve leads to an activation of the nucleus tractus solitarius (NTS), which, in turn, leads to an activation or modulation of different cortical and subcortical brain regions, including the serotoninergic raphe nuclei, the cholinergic nucleus basalis of Meynert, the pedunculopontine nucleus and the noradrenergic locus caeruleus.^8^,^13^ Accordingly, taVNS leads to a widespread modulation of different neurotransmitter systems, including the serotonergic, cholinergic and noradrenergic, but also the GABAergic system.^10 14 15^ The effects of the taVNS on these neurotransmitter systems have been demonstrated in various animal experiments.^16^,^20^ Building on these studies, several assessments were carried out on healthy volunteers, which used functional MRI(fMRI) to demonstrate the modulation of the above-mentioned neurotransmitter systems due to taVNS.^14 21^ The structures modified by taVNS, include, among others, the locus caeruleus and the NTS, but also cortical areas such as the postcentral gyrus, the cerebellum, the prefrontal cortex, the insula and the anterior cingulate.^14 21^ The interplay of these neural circuits has been shown to underlie cognitive and affective processes, such as executive function.^22^

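### The primary effect is defined in patients only, but the one model listed for it pools patients with healthy controls, so the patient effect is not isolated and its 5% level depends on the controls' variability

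*Protocol article*

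**What the plan says.** Under Outcomes, Primary, the article states: "The primary outcome measurement will be the processing speed in PwRRMS (SHAM stimulation vs verum stimulation), operationalised by the SDMT accuracy". The effect in healthy controls and the difference between the groups are listed under Secondary, as exploratory outcomes.

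Under Data analysis: "A linear mixed model will be performed for the primary/secondary outcomes using" a set of fixed effects: time (pre versus during), stimulation, "group’ (MS vs controls), ‘session order’ (Session 1 vs Session 2"), and control variables (age, fatigue, depression and severity). The random part is given only as "participant’ as random effects". No interaction and no residual covariance structure is named. On error control: "A significance level of 5% will be used to test the hypotheses".

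Two other places bear on the point. Baseline assessment says that the EDSS, the article's measure of disease severity, is used only in PwRRMS. The Discussion states the primary hypothesis more widely than the Outcomes section: "we hypothesise that taVNS will significantly improve processing speed in PwRRMS as well as in healthy controls (primary").

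**The concern.** The design is a two-session cross-over with an SDMT before and during stimulation in each session. Each patient therefore supplies a complete verum-minus-SHAM contrast, and the primary outcome as defined needs no data from controls. The model listed for it nevertheless contains both groups. Three things follow.

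- With main effects only, no parameter of the model is the effect in PwRRMS.
- If group interactions are added and the patient contrast is extracted, a common residual variance makes the patients' standard error an average over patients and controls. Equal group sizes do not protect here, because the contrast lies within one group and is not a difference between groups.
- The severity covariate has no values in controls.

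At stake is whether the primary p-value and interval carry their stated 5% and 95%, and whether they refer to patients at all.

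**Working it through.** **Inputs from the article.** 30 PwRRMS and 30 controls; four SDMT values per person; participant as the only random effect; 5% level (two-sided assumed). The sample size section gives no effect size, SD or power, so there is no power figure to reproduce. The figure that can be checked is the 5% level.

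**Assumption.** L is the patient-to-control ratio of the variance of the per-person contrast. The article does not give it; 0.5 to 3 is shown.

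**Step 1: what the listed stimulation term estimates.** Suppose stimulation changes the SDMT during stimulation by d_MS in patients and d_HC in controls, and changes nothing before stimulation. With main effects only and balanced data, the stimulation coefficient averages over two time points and two groups: (0 + d_MS + 0 + d_HC)/4. This is not d_MS unless interactions are added.

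**Step 2: the level of a patient contrast under a common residual variance.** For the contrast (during − pre under verum) − (during − pre under SHAM), with residual variance s² in each group:

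- true variance of the patient mean: 4·s_MS²/30
- variance used by the model: 4·[(s_MS² + s_HC²)/2]/30
- actual SE / model SE = f = √(2L/(L+1))
- actual level ≈ 2·[1 − Φ(1.96/f)]

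| L | f | 1.96/f | Level, formula | Level, simulated | Patients only, simulated |
|---|---|---|---|---|---|
| 0.5 | 0.816 | 2.400 | 1.6% | 1.7% | about 5% |
| 1 | 1.000 | 1.960 | 5.0% | 5.0% | about 5% |
| 1.5 | 1.095 | 1.789 | 7.4% | 7.2% | about 5% |
| 2 | 1.155 | 1.697 | 9.0% | 8.7% | about 5% |
| 3 | 1.225 | 1.600 | 11.0% | 11.1% | about 5% |

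The simulations use 30 + 30 participants and compare a pooled-variance t test (58 df) with a one-sample t test on the patients' contrasts (29 df). At L = 1 the stated 5% is reproduced. Simulating the mixed model itself gives the same pattern: 9.3% at an SD ratio of 1.5 (L = 2.25) and 12.6% at an SD ratio of 2 (L = 4).

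**Step 3: power.** At a standardised paired effect of 0.53, which 30 patients detect with 80% power, pooling at L = 0.5 gives about 68%. At L = 1 pooling gives 81.4% against 80.0% for patients only.

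**Step 4: does restricting the same model to patients restore 5%?** Not by itself. If SDMT level also varies from session to session with SD k times the residual SD, that variation cancels from the pre-to-during change but enters the residual of an intercept-only model. Of the three within-person degrees of freedom, one (between sessions) has expectation s²(1 + 2k²) and two have s². The average is s²(1 + 2k²/3).

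- k = 0.5: √(1 + 0.167) = 1.080; 1.96 × 1.080 = 2.117; level 3.4% (simulated 3.3%)
- k = 1: √(1 + 0.667) = 1.291; 1.96 × 1.291 = 2.530; level 1.1% (simulated 1.4%)

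Per-participant contrasts, or a participant-by-session random effect, avoid this.

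**Step 5: severity.** Read literally, a complete-case fit with EDSS as a covariate drops every control. Group is then inestimable and no pooling takes place. Step 2 applies once severity is given some code in controls. On either reading, the listed model cannot serve both the primary and the between-group outcome.

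**The case against.** The strongest reply is that the article nowhere says the residual variance is common. Group-specific variances fit its wording, and a condensed article may leave that choice, and the interactions, to a fuller document. This stands as far as it goes: the common variance is the default reading and not a statement. What the article does fix is the inclusion of both groups in the model used for a patients-only outcome, and a covariate that exists in one group only.

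A reader might infer that patients are bound to vary more, because the Introduction reports "cognitive impairment occurring in 40%–70% of people with RRMS" and patients differ in disability and fatigue. The article does not support that inference. Those are differences between people in level; the participant effect absorbs them and they cancel in the cross-over contrast. A simulation with the patients' between-person SD three times that of controls and equal residual variance gave a level of 5.1%. What matters is within-person or response variability, on which the article has no figure for either group.

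It can also be said that a joint model is needed for the between-group outcome and that equal variance is an ordinary assumption. Both are true, but neither requires the primary test to rest on it. Finally, the Discussion counts controls in the primary hypothesis, so the primary population is itself not settled.

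**Conclusion.** The point holds in conditional form. The listed analysis does not match the primary outcome: its stimulation term is not the effect in PwRRMS. A patient contrast taken from it under a common residual variance has a 5% level only if within-person variability is equal in the two groups. For assumed variance ratios of 0.5 to 3 the actual level would be about 2% to 11%. These ratios are assumptions and the direction is unknown: too many rejections if patients vary more, lost power if they vary less, and no distortion if they are equal.

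It would go too far to read this as showing that the trial's type I error is inflated, or that it is 11%. The article neither states a single error variance nor gives reason to place the ratio at any value. The case for a change rests on the mismatch between outcome and model and on the low cost of removing it.

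**What to change.** In Data analysis:

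- **Primary.** State that the primary analysis is fitted to the 30 PwRRMS only and tests the stimulation-by-time contrast (verum minus SHAM in the pre-to-during change), adjusted for session. Use per-participant contrasts, or add a participant-by-session random effect to the mixed model.
- **Controls.** Analyse the controls separately in the same way for the first exploratory outcome.
- **Between-group difference.** Use the joint model only here, with group interactions and group-specific variances, and without EDSS.
- **Primary population.** Reconcile the Discussion, which counts the effect in controls as primary, with the Outcomes section.

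The cost is a few sentences. If the variances are in fact equal, the critical value rises from about 2.00 (58 df) to 2.05 (29 df). The unrounded ratio is 2.045/2.002 = 1.02, so the interval is about 2% wider, and about 1 point of power is lost (81.4% to 80.0% at a standardised effect of 0.53).

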**Methods and analysis:**

This study protocol describes the prospective, single-centre, SHAM-controlled, single-blinded trial with a planned sample size of 60 participants (30 PwRRMS, with a diagnosis of multiple sclerosis according to McDonald criteria and 30 healthy controls; age: 18–50 years). The Symbol Digit Modalities Test (SDMT) will be used to determine cognitive processing speed, Beck Depression Inventory-II to determine depression and Fatigue Scale for Motor and Cognitive Functions to determine fatigue. The severity of multiple sclerosis will be assessed using the Expanded Disability Status Scale. After baseline assessment, a taVNS protocol (duration: 30 min, tolerance threshold, pulse width: 250 μs, stimulation frequency: 25 Hz, 30 s on/30 s off) will be applied, followed by post-intervention assessment.

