### Study population and recruitment

In total, 60 subjects will be included in this study, 30 PwRRMS and 30 healthy controls. PwRRMS will be recruited from the MS outpatient clinic of the University Medicine Greifswald. The healthy control group will be recruited through advertisement. Every participant will sign informed consent. An example of the participant consent form is added as online supplemental material.

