##### Expanded Disability Status Scale

The Expanded Disability Status Scale (EDSS) will be performed to evaluate the degree of disability in PwRRMS. The scale ranges from 0 to 10 and is primarily focused on motor skills.^47^ A score of 0 describes normal clinical findings whereas a score of 10 means death due to multiple sclerosis.^47 48^

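### Severity (EDSS) shares a mixed model with group but exists only for PwRRMS, so as written the model loses all 30 controls; as a control variable it also does not by itself answer secondary outcome 3

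*Protocol article*

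**What the plan says.** The protocol article's Data analysis section covers all outcomes with one sentence: "A linear mixed model will be performed for the primary/secondary outcomes using ‘time’ (pre vs during), ‘stimulation’ (taVNS vs sham), ‘group’ (MS vs controls"), followed by session order and "control variables’ (age, fatigue, depression and severity) as fixed, ‘participant’ as random effects". It names no interaction terms.

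The abstract defines severity: "The severity of multiple sclerosis will be assessed using the Expanded Disability Status Scale". The section on the scale says that it "will be performed to evaluate the degree of disability in PwRRMS". The Baseline assessment section describes an examination "consisting of SDMT, BDI-II, FSMC and EDSS (the latter only used in PwRRMS"). Age, the BDI-II and the FSMC are obtained in both groups. The article gives no EDSS value for controls and describes no separate PwRRMS-only model.

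Under Outcomes, the primary outcome is SDMT under sham versus verum in PwRRMS. Three secondary outcomes, introduced as exploratory, follow: (1) SDMT by stimulation in healthy controls; (2) the difference between the groups in the stimulation-related change; (3) "The association between disease-related variables (disease severity, fatigue and depression) and the change in processing speed". The Discussion restates the third as whether disease variables modulate the effect of stimulation.

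**The concern.** There are two mismatches between the model and the rest of the article.

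First, a covariate that one group does not have is placed beside the factor that distinguishes the groups. A likelihood-based mixed model uses only rows with complete covariates, so controls contribute nothing unless someone assigns them an EDSS value. The two secondary outcomes that involve controls then have no data behind them.

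Second, the variables whose association with change is a study question are listed only as adjusters. The coefficient of a participant-level adjuster describes differences in SDMT level averaged over the four tests. Whether people with higher EDSS, BDI-II or FSMC scores change more or less under stimulation is a different quantity.

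**Working it through.** The planned sample size plays no part in this check; only the design counts and the covariate list do.

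**Inputs.** "In total, 60 subjects will be included in this study, 30 PwRRMS and 30 healthy controls" (Study population and recruitment). "Subjects will participate in two study sessions (day 1 and day 2), in which the participants will receive either SHAM stimulation or verum stimulation" (Randomisation). Two time points per session, before and during stimulation (Data analysis). EDSS in PwRRMS only (Baseline assessment).

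**1. Rows.** Planned rows = 60 participants × 2 sessions × 2 times = 240. Rows without an EDSS value = 30 controls × 4 = 120. Complete rows = 240 − 120 = 120, from 30 participants, with 0 controls.

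**2. Estimability.** Take the fixed effects as a bare list: intercept, time, stimulation, group, session order, age, fatigue, depression, severity = 9 columns. With PwRRMS only, group equals the intercept, so the rank is 8. Add the interactions among time, stimulation and group that outcome 2 needs (4 more columns): 13 columns. Group and its three interactions now duplicate the intercept, time, stimulation and time × stimulation, so the rank is 13 − 4 = 9. A constructed design matrix gave the same result, 13 columns and rank 9. No group term is estimable under either reading.

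**3. What survives.** All 30 PwRRMS keep all four rows, so time × stimulation in PwRRMS remains estimable. Adding EDSS as a main effect changed that estimate by less than 1e-13 in simulation, as expected for a covariate that is constant within participant.

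**4. Controls coded EDSS 0.** All 240 rows stay and the rank is 13. Over 100 simulated trials, time × stimulation × group was unchanged to rounding error. The group coefficient averaged −5.5 (mean SE 3.7), against −9.5 (mean SE 2.7) without EDSS, because it now compares controls with a patient at EDSS 0. The article describes 0 as normal clinical findings, so it is also a possible patient score.

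**5. Level versus change (outcome 3).** PwRRMS-only simulations, 200 runs per scenario. Assumed values, not from the article: EDSS spread evenly over 0 to 6, level slope −1.5 SDMT points per EDSS point, participant SD 8, residual SD 4.

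| True modulation (SDMT points per EDSS point) | EDSS main effect significant | time × stimulation × EDSS significant |
|---|---|---|
| 0 | 39% | 3.5% |
| 1.5 | 28% | 48% |

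The main effect rejects less often when modulation is present. Modulation acts in one of the four tests, so the average level slope becomes −1.5 + 1.5/4 = −1.125, which is nearer zero. The main effect follows level; only the interaction follows change.

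**The case against.** The strongest reply on the first part is that the loss is conditional. The article neither states nor excludes a structural value for controls, and a code of 0 leaves intact the term that outcome 2 needs. A simulated check with EDSS centred at the MS mean and controls set to 0 also left time × stimulation × group identical, with a group coefficient of −9.57 against −9.54 without EDSS. No listed outcome uses the group main effect. All of this stands: it shows that the model can be rescued. It does not show that the article specifies the rescue.

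One may also read the sentence as separate fits per outcome, since the primary outcome and outcome 1 each concern one group. That does not help unless severity is also dropped. A controls-only fit that requires EDSS has no rows, and outcome 2 needs both groups.

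On the second part, the article names no interaction at all, not even time × stimulation. Such terms are commonly left to a full analysis plan, which is not shown. A reader might infer that the trial will test disease variables through main effects and report a level correlation as modulation. The documents do not support that: the Discussion states the modulation aim plainly, and interactions may be specified elsewhere. What stands is narrower: the assigned role of control variable does not match the stated aim.

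A reader might also infer that the primary analysis is compromised, especially as the Discussion mentions healthy controls in the hypothesis that it labels primary. The Outcomes section restricts the primary outcome to PwRRMS, and that contrast keeps all its data.

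**Conclusion.** The point holds at moderate severity. As written, the joint model combines group with a covariate that controls do not have. Fitting it with EDSS missing removes 30 of 60 participants and 120 of 240 rows, and secondary outcomes 1 and 2 cannot be estimated. This rests on two conditions: controls receive no EDSS code, and rows with a missing covariate are excluded. Only severity causes the loss. The row counts assume that every participant completes both sessions.

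For outcome 3, the listed role of severity, fatigue and depression is insufficient by itself. The simulated percentages illustrate the gap between level and change under assumed values and do not forecast this trial's error rate. They treat the covariates as fixed per participant; day 2 repeats the day 1 protocol, so BDI-II and FSMC may be measured twice and the value to be used has to be named.

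The consequences are confined to outcomes that the article calls exploratory, which is why the point is not graded higher.

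**What to change.** 1. Remove severity from every model that includes controls. All 240 planned rows and the group terms then become usable. If the sponsor prefers to keep it, the code for controls and the resulting meaning of the group coefficient must be stated.
2. Answer secondary outcome 3 in a PwRRMS-only model. Let each disease variable (EDSS, BDI-II, FSMC), taken as the first-session value before stimulation, interact with time × stimulation. Equivalently, for each participant compute D = (during − pre) under verum − (during − pre) under sham, and regress D on each variable.
3. State that the coefficient reported for outcome 3 is this interaction (or the slope of D), and that any main effect of a disease variable describes SDMT level only.

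The cost is a few lines of analysis text. The measurements needed are already scheduled for collection, and neither visits nor sample size change.
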